The present study will address a number of the limitations of previous studies. Primarily, the current sample will be sufficiently large to detect treatment effects (see Power analyses below) and will involve an RCT with an appropriate control group for this stage of the clinical trial process. The selection of a wait-list control condition was based upon consideration of the literature and a lack of consensus regarding an acceptable attention control condition to compare to yoga. In this preliminary study, the control group will involve patients receiving care as usual for the length of the yoga intervention. Symptoms, physical activity, and lifestyle changes will be assessed weekly in both the yoga and control groups. While the control group will not account for the social, attention, or expectation aspects of the IYP, a usual care control group is appropriate at this stage of the research when examining a novel treatment in an untested population. If the IYP is found to be superior to the wait-list group in this exploratory study, a future R01 will incorporate a control condition that accounts for the social, attention, and expectation effects of a group-based intervention.

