## Research design and methods

### Design

A randomized control design will be used to examine the impact of IY for youth aged 14-26 years with IBS on the following outcomes: IBS symptoms, global improvement, HRQOL, and laboratory pain sensitivity. The study design is depicted in Figure 2. After baseline assessment, including standardized questionnaires and the laboratory visceral task (including ANS/psychophysiological measurements and cortisol collection), participants will be randomly assigned to the IY program or the wait-list control group. It is anticipated that randomization will ensure equal distribution of males and females, adolescents and young adults, and symptom severity across groups. Baseline assessments will be completed in order to ensure that the yoga and control groups are comparable, and to test for pre/post changes in the yoga group.

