### Additional measures

**1**. An **expectation **question will be administered after assignment and before treatment to assess whether treatment expectation impacts outcomes. Subjects will be asked to rate on a scale of 0 to 10 'How much do you think the treatment will benefit you or improve your IBS symptoms?'

**2**. The **weekly monitoring form **will include items related to mood, IBS pain, symptoms and functioning and use of any new interventions. The form will be administered by telephone or e-mail at the end of each week to both groups. The weekly monitoring form is an important tool in the study design, given that IBS is a condition without clear biomarkers to assess illness severity and progression, self-reported pain, symptom and functioning tools will form the basis for assessment of appropriate dose. The form will also ensure the control group does not introduce any new mind-body treatments during the intervention.

**3**. Females will receive a question that asks about their last menstrual period (LMP) to control for potential varying pain sensitivity over cycle phase. Self-reported menstrual cycle length is a common, non-invasive clinical marker for reproductive function [122].

Participant Burden: It is anticipated that the laboratory procedure and the standardized questionnaires will take 1.5 hours at baseline, and 1.5 hours post-treatment. The 2-month follow-up is expected to take 40 minutes. The weekly monitoring form will take approximately 8-10 minutes each week.

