### Data analyses

Each stage of data analysis detailed below will be carried out separately for adolescent (14-18 yrs) and young adult (19-26 yrs) sub-groups. If no differences are found, the groups will be combined. It is unlikely that differences will emerge in terms of feasibility, efficacy or safety, but a separate analysis of sub-groups will ensure that findings are generalizable across the ages studied.

Once the data set has been cleaned and examined for skewness, exploratory data analyses will be conducted using univariate methods to describe the variables of interest and bivariate techniques to characterize their interrelationships within our sample. Continuous variables will be summarized over time in each group using means, medians, range, interquartile range and standard deviations. Cross tabulated frequencies will be given for all discrete variables by group and time. Both parametric and non-parametric correlations will be reported. Expectation ratings will be correlated with primary outcomes to determine whether patient expectations were related to post-intervention symptoms.

For **Hypothesis 1**: IY will be safe, acceptable and feasible: more than 80% of subjects will complete the training program, the frequencies of drop-outs for the IYP and control groups will be examined. Attrition rates will be compared between the yoga and control groups; demographics and baseline values of functioning between those who complete the protocol and those who do not will also be compared. If drop-outs are random, then the results may be considered unbiased. If drop-outs are not random, the direction and magnitude of potential biases will be considered.

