#### Sample size determination and power analysis

Based on our previous pilot work using Iyengar yoga for patients with rheumatoid arthritis [82], we estimated that yoga was likely to have a medium effect size on the primary outcomes. For power calculations, a freely-available software for power calculations - G*Power 3- was used to estimate the sample size needed for the estimated effect size using a pre/post by group interaction. Pairing a medium effect size with a range of correlation values (.10 to .50) for baseline and follow-up scores resulted in power calculations ranging from 60 to 34 total subjects. These calculations used a Type I error rate of α = .05, and statistical power of 0.80 (the Type II error rate, 1- β). We settled upon the middle value of 47 total subjects. Assuming a 20% attrition rate, it was estimated that 60 total subjects would need to be recruited (30 per group).

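### The expectation check has no stated conditioning on arm, so a pooled correlation could arise from arm differences alone

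*Protocol article*

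**What the plan says.** The article's Additional measures section describes a single 0 to 10 item: "How much do you think the treatment will benefit you or improve your IBS symptoms". On timing and purpose it says this "question will be administered after assignment and before treatment to assess whether treatment expectation impacts outcomes". Under Design, "participants will be randomly assigned to the IY program or the wait-list control group", so allocation is known to participants when they answer.

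The analysis is one sentence in the Data analyses section: "Expectation ratings will be correlated with primary outcomes to determine whether patient expectations were related to post-intervention symptoms". It sits in the exploratory paragraph, which speaks of "bivariate techniques to characterize their interrelationships within our sample". In the same paragraph the continuous summaries are given by group and the frequencies by group and time. The only split announced for all analyses is by age: "Each stage of data analysis detailed below will be carried out separately for adolescent (14-18 yrs) and young adult (19-26 yrs) sub-groups".

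The section Yoga as treatment for IBS is open about the limits of the comparator: "While the control group will not account for the social, attention, or expectation aspects of the IYP". No other assessment of expectation is described.

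**The concern.** One arm rates its expectation knowing that yoga is about to start; the other answers knowing that it has been assigned to wait. A difference in mean expectation is therefore plausible, and the trial is designed to find a difference in mean outcome. If both differences exist, plotting all participants together gives two clouds of points displaced along both axes. A correlation appears even if expectation is unrelated to outcome inside each cloud.

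The primary outcomes are all self-reported questionnaires and the control does not match expectation, so this correlation is the only information the trial offers on that source of bias. If it comes out positive merely because the arms differ, a reader may conclude that expectation explains the symptom results when the data show nothing of the kind. That could also misdirect the later trial, for which the protocol foresees a control that accounts for expectation.

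**Working it through.** **The plan's own figures.** The plan gives no figure for the expectation correlation. It does give the sample size used below, which I checked first. The plan says "we estimated that yoga was likely to have a medium effect size on the primary outcomes". Taking medium as f = 0.25 for a two-group, two-time interaction, the noncentrality is N·f²·2/(1 − ρ), with alpha 0.05 and power 0.80.

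- ρ = 0.10 gives 59, or 60 with equal groups; the plan says 60.
- ρ = 0.50 gives 34; the plan says 34.
- The midpoint is (60 + 34)/2 = 47, as stated.
- 47/0.8 = 58.75, so 59; the plan recruits 60, 30 per arm.

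**Inputs for the check.** From the plan: equal arms, 47 analysed or 60 recruited, alpha 0.05. Assumed: an outcome gap dY of 0.5 SD as one reading of a medium effect, with 0.8 and 1.0 as larger cases; an expectation gap dE of 1 or 2 SD, because the document gives none; zero association within each arm. Outcomes are oriented so that higher is better. For a scale where lower is better the sign flips and the size is unchanged.

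**Formula.** With 1:1 arms and within-arm SD of 1:

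r = (dE/2)(dY/2) / √[(1 + dE²/4)(1 + dY²/4)]

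- dE = 1, dY = 0.5: 0.5 × 0.25 / √(1.25 × 1.0625) = 0.125/1.152 = 0.108
- dE = 2, dY = 0.5: 1 × 0.25 / √(2 × 1.0625) = 0.25/1.458 = 0.171
- Ceiling as dE grows without limit, dY = 0.5: 0.25/√1.0625 = 0.243

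**Rejection rates**, from 20,000 simulated trials per setting:

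| dE | dY | pooled r | pooled, n = 47 | pooled, n = 60 | arm-adjusted, n = 47 |
|---|---|---|---|---|---|
| 1 | 0.5 | 0.11 | 11% | 13% | 5.3% |
| 2 | 0.5 | 0.17 | 22% | 26% | 5.1% |
| 1 | 0.8 | 0.17 | 20% | 25% | 4.9% |
| 2 | 0.8 | 0.26 | 45% | 55% | 5.0% |
| 1 | 1.0 | 0.20 | 28% | 34% | 5.1% |
| 2 | 1.0 | 0.32 | 62% | 73% | 4.9% |

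If the arms do not differ on expectation, or do not differ on outcome, the pooled rate stays at about 5%. The ceiling on r is 0.37 at dY = 0.8 and 0.45 at dY = 1.0. Splitting by age does not help, because each age group would normally contain both arms.

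**Power after conditioning on arm.** By Fisher's z, power is 1 − Φ(1.96 − atanh(r)·√(n − 3)). For a true within-arm r of 0.3 and n = 30, atanh(0.3)·√27 = 0.3095 × 5.196 = 1.608, so power is 36%. At n = 24 it is 29%. For r = 0.4 the figures are 60% and 49%; for r = 0.5 they are 81% and 71%. A single arm-adjusted term, assuming the same association in both arms, uses √(n − 4). For r = 0.3 it gives 0.3095 × √56 = 2.316, or 64%, at n = 60, and 0.3095 × √43 = 2.030, or 53%, at n = 47.

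**The case against.** The strongest reply is that the protocol never says the arms are pooled. The phrase about the sample belongs to the general bivariate exploration, not to the expectation sentence, and an article may leave stratification of a descriptive correlation to a fuller document. This stands in part: pooling is an inference. It is still the natural reading. The same paragraph names the group where it means to split by it, and the regressions for Hypothesis 4 explicitly include group and its interaction with the mediator. The expectation sentence names a method and a purpose, and the method as named does not serve the purpose.

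A second reply is that the text permits a different schedule. The Randomization section has eligible controls taking the yoga programme after six weeks and repeating the assessments. They might be asked just before that and their answers related to symptoms after yoga, which would avoid this comparison. The document does not settle it. If instead such a late rating were related to the control-period outcome, it would come after the outcome it is meant to explain. The ambiguity is a reason to clarify.

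A reader might infer that rating after assignment is itself the fault. The documents do not support that. In an open trial, expectation once the arm is known is arguably what could colour self-report. The weakness lies in correlating across arms without conditioning.

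Finally, the analysis is exploratory, tests none of the four hypotheses and enters no primary model, and the protocol makes no claim that it resolves expectation bias. All of that is true, and it limits the weight of the point.

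**Conclusion.** The point holds in a limited form. As most naturally read, the planned correlation can be produced by arm differences alone. At an outcome gap of 0.5 SD and an expectation gap of 1 to 2 SD, it would be significant in about 11% to 22% of trials with 47 analysed when there is no association within either arm. The expectation gap is assumed, and the higher rates in the table need outcome effects of 0.8 to 1.0 SD, beyond the 0.5 SD taken here for a medium effect.

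A reader might go further and conclude that the expectation check cannot be interpreted at all. That is not supported. The artefact needs a gap on both variables. At a 0.5 SD outcome gap it cannot exceed r = 0.24, so a clearly larger correlation would need another explanation. The same data analysed by arm, or adjusted for arm, bring the false-positive rate back to about 5%. The primary treatment comparison is unaffected.

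**What to change.** Keep the rating after assignment. State that its association with each primary outcome will be estimated within each arm, or as an added term in the Hypothesis 2 ANCOVA alongside arm and the baseline score. The global improvement scale is itself a comparison with study entry and has no baseline score, so arm alone would serve there. State that a correlation pooled across arms will not be interpreted. Define what the treatment refers to for wait-list participants (usual care or the deferred programme), and say when they are asked and which assessment their rating is related to.

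The cost is one model term and two clarifying sentences, with no new data. The downside is modest power, about 36% within one arm of 30 for a true r of 0.3, so estimates should carry confidence intervals and a null result should not be read as reassurance. Even the repaired analysis cannot separate expectation from the effect of yoga, because the control does not match it. A further item before randomisation is optional: it would be free of allocation, but it would not capture how expectation shifts once the arm is known.

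### Comparing attrition and baseline values cannot show that drop-out is random, so it cannot support treating the results as unbiased

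*Protocol article*

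**What the plan says.** The Data analyses section, under Hypothesis 1, compares attrition rates between the yoga and control groups. It adds that "demographics and baseline values of functioning between those who complete the protocol and those who do not will also be compared". A rule with two branches follows. The first branch reads: "If drop-outs are random, then the results may be considered unbiased". In the second, if drop-outs are not random, the direction and size of possible bias are to be considered. The section gives no criterion for random and lists no other evidence for it.

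Other parts of the protocol bear on this:

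- **Sample size determination and power analysis** plans on 60 patients, 30 per group, "Assuming a 20% attrition rate".
- **Data analyses, Hypothesis 2** uses baseline-adjusted ANCOVA. An intent-to-treat analysis with last observation carried forward (LOCF) is to confirm the findings in completers.
- **Data management** promises sensitivity analyses after imputation and names no method.
- **Additional measures** describes a weekly monitoring form that covers symptoms: "The form will be administered by telephone or e-mail at the end of each week to both groups". Its data are used for exploratory analyses (Hypothesis 4) and for safety reports (Content of safety reports), where reasons for loss to follow-up are also tabulated. None of this feeds the drop-out judgement.

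**The concern.** Whether completer results are unbiased depends on whether leaving is related to how patients fare after randomization. The listed comparisons do not address that. Patients who leave the yoga arm because they are not improving can resemble completers at baseline, and they can be matched in number by control patients who leave for unrelated reasons. The rule would then point to the first branch although the completer comparison favours yoga.

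The trial compares an open group class with a waiting list and uses self-reported primary outcomes, so drop-out linked to poor response in one arm is a plausible threat. The Significance section says the findings are to supply effect sizes for larger studies, so a bias passed as absent would carry forward into their planning.

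**Working it through.** **1. The plan's own numbers.** Take a medium effect as f = 0.25 in the pre/post by group interaction, with noncentrality N × 2 × f² / (1 − ρ).

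- ρ = .10, N = 60: 60 × 2 × 0.0625 / 0.90 = 8.33, power 0.81.
- ρ = .50, N = 34: 34 × 2 × 0.0625 / 0.50 = 8.50, power 0.81.
- Midpoint (60 + 34) / 2 = 47, and 47 / 0.8 = 58.75. This rounds up to 59, or 60 with equal arms.

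The plan's 60 is reproduced. Twenty percent of 60 is 12 drop-outs, leaving 48 completers, or about 6 and 24 in each arm if losses are equal.

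**2. Power of the baseline comparison.** The two-sided .05 level is an assumption. For a two-sample t test the noncentrality is d × √(n₁n₂ / (n₁ + n₂)). With d = 0.5 and 12 versus 48 this is 0.5 × √(576 / 60) = 1.55, against a critical value of 2.00 on 58 df.

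| Baseline difference, 12 vs 48 | Power | Missed |
|---|---|---|
| 0.3 SD | 15% | 85% |
| 0.5 SD | 33% | 67% |
| 0.8 SD | 68% | 32% |
| 1.0 SD | 86% | 14% |

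Power reaches 50% at 0.64 SD and 80% at 0.92 SD. The 95% CI half-width is 2.00 × √(1/12 + 1/48) = 0.65 SD. Within one arm (6 vs 24) a 0.5-SD difference is missed 82% of the time. At other drop-out counts, power at 0.5 SD is 21% (6 vs 54) and 42% (18 vs 42). The protocol also runs each analysis stage separately by age group, which makes these comparisons smaller still.

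**3. Power of the attrition comparison.** Exact enumeration with 30 per arm and attrition of 30% versus 10% (9 + 3 = 12 losses) gives power of 50% by chi-square and 37% by Fisher's test. The difference is therefore missed 50% to 63% of the time.

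**4. What informative drop-out does.** The drop-out mechanisms here are assumptions; the protocol gives no figures for them. The simulations had no true effect, 30 per arm, baseline correlation .1 to .5, and baseline-adjusted ANCOVA. In the LOCF analysis the baseline score was carried forward, with no time trend.

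| Assumed drop-out | Completer bias toward yoga | False favourable result (nominal 2.5%) | Bias with LOCF |
|---|---|---|---|
| Milder: log-odds +1 per SD worse response, yoga arm only | about 0.15-0.18 SD | about 9% | about 0.12-0.15 SD |
| Worst case: the 6 worst responders leave yoga, 6 random patients leave control | about 0.3 SD (0.29-0.34) | about 26% | about 0.23-0.27 SD |

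An intermediate case (6 yoga drop-outs with mainly, but not strictly, the worst course; correlation .5) gave a bias of 0.20 SD. In it a t test of one baseline score between drop-outs and completers rejected in 5% of trials, its nominal level, so that test carried no information about the bias.

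LOCF removes about a fifth: from 0.33 to 0.26 SD, for example, is a reduction of 0.07 / 0.33 = 21%. False favourable results under LOCF stayed at about 22-25% in the worst case and 9% in the milder one.

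**The case against.** The strongest reply is that the sentence is a conditional and is true as it stands: completely random drop-out does not bias the comparison, and the text says only that results may be so considered. That stands. The fault lies in the evidence offered for the condition.

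Several stronger readings are tempting, and the protocol does not support them.

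- **That randomness is judged by p > .05.** No criterion is given. The miss rates therefore rest on an assumption, but the inability of baseline data to reveal outcome-related drop-out does not.
- **That consideration of bias is switched off.** The LOCF analysis and the sensitivity analyses after imputation do not depend on this rule. They soften its consequence without repairing it: LOCF leaves about four fifths of the simulated bias, and an imputation method that assumed random drop-out would share the flaw.
- **That the check would nearly always pass.** With one baseline test and one attrition test it passes in 90-95% of simulated trials. The protocol compares several variables. With eight baseline variables (assumed correlation 0.3 with the first, all p > .05 required) it passes in roughly two thirds, and with twelve in just over half. The extra failures are chance alarms, so the check is still uninformative.
- **That a 26% false favourable rate is to be expected.** It requires exactly the six worst yoga responders to leave while control losses are purely random. It is an upper illustration.
- **That symptom course is never examined.** Weekly data and reasons for loss are reviewed elsewhere, though not for this judgement.

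It is also fair to say that the sentence sits under a feasibility hypothesis in a study the authors call preliminary and exploratory. That tempers the weight of the point, but the sentence speaks of the results in general.

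**Conclusion.** The point holds in a limited form. The listed comparisons cannot support the inference from apparently random drop-out to unbiased results at any sample size, and at the planned size they are weak even for what they do measure: about 67% of 0.5-SD baseline differences are missed, and 50% to 63% of attrition differences of 30% versus 10%, at an assumed two-sided .05. Under assumed drop-out of poor responders in the yoga arm only, the completer analysis could be off by about 0.15-0.18 SD, or about 0.3 SD at worst, and LOCF would often confirm it. How large the bias would be in this trial cannot be known from the document. The sentence should be changed; the design and the data collection need no change.

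**What to change.** 1. Delete the sentence that lets results be considered unbiased when drop-outs are random.
2. Report attrition by arm and completer/non-completer differences as estimates with 95% CIs, and state that they are not used to conclude absence of bias.
3. Describe drop-outs by arm with their last weekly-monitoring symptom scores and their reasons for loss.
4. Whatever these show, make one of the sensitivity analyses promised under Data management an IBS-SSS analysis that assumes drop-outs did worse than completers by stated amounts. A delta-adjusted analysis is one example, and another method with the same assumption would serve.

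The cost is a change of wording and a little extra analysis of data already being collected. The downside is that the trial can no longer state, on this basis, that its results are unbiased.

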To test **Hypothesis 2: **Participants in the IY group will demonstrate significantly greater improvement in IBS symptoms, global improvement and HRQOL apparent immediately post-intervention and at the 2- month follow-up. Consistent with recommendations regarding analyses for randomized trials, analysis of covariance (ANCOVA) will be used to test group differences [123]. The baseline scores of the outcome variables will be entered as independent variables. The Next, analyses will assess maintenance of treatment gains during the follow-up period. Changes in IBS symptoms, HRQOL and improvement across baseline, post-treatment and follow-up will be evaluated using ANCOVAS. An intent-to-treat (ITT) analysis on the primary outcome measures will be conducted to confirm findings in treatment completers by including all participants who enrolled in the study, using the last observation carry forward approach. Even if significant differences are noted, consideration will be given to established minimally clinically significant differences on outcome measures between the groups. Thus, in order to be considered a clinically meaningful difference, participants must evidence a decrease in at least 50 points on the IBS-SSS in comparison to controls.

To test **Hypothesis 3: **Participants in the IY group will report significantly reduced visceral sensitivity, disability and improved psychospiritual functioning. The same methods will be used as described above for hypothesis 2. Similar analysis will be conducted to examine changes in visceral sensitivity, disability and psychospiritual functioning, including self-efficacy, coping, mood, acceptance and mindfulness from baseline to post-treatment.

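### The lead efficacy comparison is made in completers, and the LOCF intent-to-treat analysis meant to confirm it is a weak check on drop-out bias

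*Protocol article*

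**What the plan says.** Under Data analyses, Hypothesis 2 is tested by ANCOVA adjusted for the baseline score, at post-treatment and again to see whether gains last to 2 months. The intent-to-treat analysis covers the primary outcomes only, and its purpose is "to confirm findings in treatment completers by including all participants who enrolled in the study, using the last observation carry forward approach". Hypothesis 3 (secondary outcomes) takes over the same methods. Nowhere does the protocol make the comparison of all randomised participants primary.

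Three other provisions bear on missing data:

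- Data analyses, Hypothesis 1: attrition is compared between arms, and completers are compared with non-completers on demographics and baseline functioning. Then: "If drop-outs are random, then the results may be considered unbiased". If drop-out is not random, the direction and size of possible bias are to be considered.
- Data management: sensitivity analyses with missing values imputed, no method named.
- Design (text under Randomization): every participant is to repeat the baseline assessments at the end of the 6-week period.

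The sample size section allows for drop-out only as lost numbers: "Assuming a 20% attrition rate", 47 becomes 60.

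**The concern.** An analysis done to confirm a completer result makes the completer result the finding. Completing is decided after randomisation and does not mean the same thing in the two arms. The yoga arm is asked to attend two 1.5-hour classes a week for 6 weeks, and the control arm waits under usual care. If those who leave the yoga arm differ in outcome from those who stay, the completer comparison no longer has the protection of randomisation.

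LOCF then has to catch the problem, and it makes a different assumption at each time point. A missing post-treatment score is replaced by baseline, which assumes no change. A missing 2-month score is replaced by the post-treatment score, which assumes the gain was kept, and that is what the follow-up analysis is meant to find out. The Global Improvement Scale, a primary outcome, asks about change since study entry, so there is nothing to carry forward when its post-treatment value is missing.

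At stake are the main efficacy claim and the effect size that the Significance section intends for planning larger trials.

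**Working it through.** **1. The plan's own figure.** The inputs come from the sample size section. The effect is given in words ("we estimated that yoga was likely to have a medium effect size on the primary outcomes"), so Cohen's f = 0.25 is assumed. The test is the one "needed for the estimated effect size using a pre/post by group interaction". The plan's range is: "range of correlation values (.10 to .50) for baseline and follow-up scores resulted in power calculations ranging from 60 to 34 total subjects". Error rates: "These calculations used a Type I error rate of α = .05, and statistical power of 0.80".

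The noncentrality is f² × N × 2 / (1 − r), with 1 and N − 2 degrees of freedom.

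- r = 0.10: the smallest N is 59, or 60 with equal arms (noncentrality 0.0625 × 60 × 2 / 0.9 = 8.33).
- r = 0.50: N = 34 (0.0625 × 34 × 2 / 0.5 = 8.5).
- Midpoint: (60 + 34)/2 = 47. Then 47/0.8 = 58.75, so 59, or 60 with equal arms.

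The stated sample size reproduces and is not in question. With 60 × 0.8 = 48 completers, power is 0.71, 0.82 and 0.92 at r = 0.1, 0.3 and 0.5.

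**2. Completer ANCOVA at post-treatment.** Assume no true effect, 20% drop-out per arm, and controls leaving at random. Yoga drop-out has correlation c with the part of a poor outcome that baseline does not explain. Losing the worst 20% of a normal distribution shifts the mean by φ(0.842)/0.8 = 0.35 SD. After baseline adjustment the bias is c × 0.35 × √(1 − r²).

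- c = 0.5: 0.5 × 0.35 × 0.954 = 0.17 at r = 0.3, and 0.5 × 0.35 × 0.866 = 0.15 at r = 0.5.
- c = 1 (extreme): 0.33 and 0.30.

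**3. LOCF at post-treatment.** With equal drop-out q and baseline carried forward, the estimate is (1 − q) times the completer estimate. LOCF therefore keeps 80% of the completer bias when q = 0.20.

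Simulation of both analyses (30 per arm, 4000 runs per scenario, no true effect, 20% drop-out per arm). Each cell gives r = 0.3 / r = 0.5, and bias is in SD toward yoga:

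| Yoga drop-out | Completer bias | Type I error | LOCF bias | Type I error |
|---|---|---|---|---|
| Random | 0.00 / 0.00 | 5.8% / 5.0% | 0.00 / 0.00 | 5.6% / 5.1% |
| c = 0.5 | 0.16 / 0.15 | 8.7% / 9.7% | 0.13 / 0.12 | 8.1% / 9.1% |
| Worst 20% leave | 0.33 / 0.31 | 24.8% / 26.4% | 0.26 / 0.25 | 22.0% / 25.7% |

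Two further LOCF results:

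- Random 20% drop-out with a true effect of 0.50 SD: 0.8 × 0.50 = 0.40 SD, while completers give 0.50.
- Both arms improve 0.5 SD, no true difference, random drop-out of 33% in yoga and 7% in control (assumed rates): 0.67 × 0.5 − 0.93 × 0.5 = −0.13 SD, against yoga. With the rates swapped, 0.13 SD in favour of yoga.

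**4. LOCF at 2 months.** Suppose the whole yoga gain is truly lost, and a fraction q of the yoga arm has a post-treatment score but no follow-up score. LOCF still shows q × gain as kept: 10%, 20% or 40% of it for q = 0.10, 0.20 or 0.40.

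**5. The drop-out check.** At 20% of 60 there are 12 drop-outs and 48 completers. The baseline difference detectable with 80% power at two-sided 5% is 2.80 × √(1/12 + 1/48) = 2.80 × 0.323 = 0.90 SD. Even a sensitive baseline comparison could not show that drop-out is unrelated to the unseen outcome.

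**The case against.** The other side has real points. The trial calls itself preliminary and exploratory, and it does pre-specify an analysis of everyone enrolled for the primary outcomes. It also plans imputation in sensitivity analyses, compares attrition between arms, and asks all participants to repeat the assessments. Unnamed imputation details may properly sit in an analysis plan that is not shown. If drop-out depends only on arm and the adjusted baseline score, completer ANCOVA is not biased at all.

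All of that stands, and it narrows the point without removing it. Imputation belongs to the sensitivity analyses and does not change which result leads.

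A reader might infer more than the protocol supports:

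- That a completer is someone who attended all 12 classes. Twelve are scheduled, but no attendance threshold is stated.
- That patients who find yoga unhelpful will be the ones to leave. This is plausible, but the document names only independence and transport as influences on attendance and retention.
- That LOCF assumes the result under test throughout. This holds only for missing 2-month scores. At post-treatment it assumes no change and can work against yoga.
- That similar baselines alone certify an unbiased result. The protocol does not define random drop-out and also provides for the non-random case. The fair criticism is that the planned comparisons cannot support the inference.

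**Conclusion.** The point holds in this form: the plan leads with completers and supports that result with a method too weak to confirm it. Bias is not demonstrated; the lead estimate is left open to it. Under the assumed moderate mechanism (c = 0.5), the completer estimate moves 0.15 to 0.16 SD toward yoga and type I error roughly doubles to 9 to 10%. LOCF moves 0.12 to 0.13 SD the same way, so agreement between the two would reassure little. The worst-20% figures are an extreme case, and under purely random drop-out the completer bias is zero. Only the 20% rate comes from the protocol. The drop-out mechanism, the unequal drop-out rates and f = 0.25 are assumptions; the baseline-outcome correlations of 0.3 and 0.5 lie within the plan's own range.

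**What to change.** - **Primary analysis:** all randomised participants in their assigned arm, by baseline-adjusted ANCOVA after multiple imputation by arm, or by a likelihood-based mixed model. Use the weekly monitoring scores as auxiliary variables, and keep the imputation model small at 30 per arm. Imputing from baseline alone would add little to the completer ANCOVA. The gain comes from the weekly scores and from outcomes obtained from people who stop attending.
- **Data collection:** state that the repeat assessments for all participants include those who stop attending classes.
- **Completers:** define the term and make that analysis supportive.
- **LOCF:** replace it, and say how a missing Global Improvement Scale value is handled.
- **Drop-out description:** keep the comparisons of attrition and baseline characteristics as description, and delete the step from random drop-out to unbiased results.
- **Sensitivity analysis:** use the one already promised under Data management for a named not-at-random scenario, for example yoga drop-outs imputed from the control mean at post-treatment. This is needed because missing-at-random methods do not by themselves remove the bias illustrated above.

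The cost is plan wording, modest programming and possibly a less favourable estimate. Recruitment stays at 60.
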